## 1.2 Supplementary Note 2: Factor Analysis of CANTAB Cognitive Tests

### 1.2.1.1 Factor analysis/correlation, Method: principal factors

| Factor  | Eigenvalue | Difference | Proportion | Cumulative |
|---------|------------|------------|------------|------------|
| Factor1 | 2.39168    | 2.10609    | 0.9194     | 0.9194     |
| Factor2 | 0.28559    | 0.05551    | 0.1098     | 1.0292     |
| Factor3 | 0.23008    | 0.23512    | 0.0884     | 1.1177     |
| Factor4 | -0.00504   | 0.07484    | -0.0019    | 1.1157     |
| Factor5 | -0.07988   | 0.14125    | -0.0307    | 1.085      |
| Factor6 | -0.22113   | .          | -0.085     | 1          |

### 1.2.1.2 Factor loadings (pattern matrix) and unique variances:

| Variable                        | Factor1 | Uniqueness |
|---------------------------------|---------|------------|
| Executive function (OTS)        | 0.213   | 0.9546     |
| PAL: first attempt memory score | 0.9439  | 0.1090     |
| PAL: total errors               | 0.9183  | 0.1568     |
| Pattern recognition memory      | 0.5116  | 0.7382     |
| Spatial span                    | 0.4875  | 0.7624     |
| Spatial working memory          | 0.3357  | 0.8873     |

### 1.2.1.3 Scoring coefficients

| Variable                        | Factor1 Scoring coefficients (method = regression) |
|---------------------------------|----------------------------------------------------|
| Executive function (OTS)        | 0.02319                                            |
| PAL: first attempt memory score | 0.5411                                             |
| PAL: total errors               | 0.35486                                            |
| Pattern recognition memory      | 0.05789                                            |
| Spatial span                    | 0.10573                                            |
| Spatial working memory          | 0.00626                                            |

CANTAB: Cambridge Neuropsychological Test Automated Battery. OTS: One Touch Stockings of Cambridge cognitive test. PAL: Paired Associates Learning.

## 2 Supplementary Figures

### 2.1 *Supplementary Figure S1: Read Quality and Read Mapping for all Microbiome Samples.*

[figure not shown]

Barplots summarizing read quality and read mapping for all samples. M = millions of reads. Samples are ordered by increasing number of mapped reads.

## 2.2 Supplementary Figure S2: Broad Sense Heritability of Taxa

[figure not shown]

The model was fitted to the relative abundance of different taxa (*abundance* ~ 1). Only taxa with broad-sense heritability larger than 0.01 and with prevalence of 2 in twin-pairs were chosen to be included in the figure. The solid line marks the heritability value of 0.2, and the dashed line marks the mean heritability of the taxa shown in the figure. Taxa with heritability value > 0.2 are shown in brown.

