Pairwise comparisons of microbiota (dis)similarity were compared using the Mann-Whitney U test and verified by comparing the Mann-Whitney U test statistic obtained when analysing data with the original group labels to the test statistic distribution obtained by 1,000 group label permutations. The latter comparison was also performed using the Mann-Whitney U test.

Unless otherwise stated, permutational multivariate analysis of variance (PERMANOVA) tests were performed using the `adonis2` function from the `vegan` R package with 1000 permutations and `by = "margin"`, thus assessing the marginal effects of the terms (i.e. each marginal term analysed in a model with all other variables). Multivariate homogeneity of group dispersions was tested using the `betadisper` and `permutest` functions from the `vegan` R package with 1000 permutations and `type = "spatial median"`, which is an implementation of the PERMDISP2 procedure from^12. Distance-based redundancy analysis (dbRDA) tests were performed using the `capscale` function from the `vegan` R package with 1000 permutations and `"sqrt = T"` to prevent negative eigenvalues. With 1000 permutations, the lowest possible P value is  $1/1001 = 0.000999$ .

When performing statistical testing on multiple hypotheses, we used the Benjamini–Hochberg (BH) method to control the false discovery rate (FDR) at a level of 10%. Thus, of all the “statistically significant” associations we report in this context, we expect 10 % of these to be false associations (arising due to chance). When we report the “FDR-adjusted P value”, this is not a P value per se, but rather indicates the FDR at which a given hypothesis would be called significant using the BH method. FDR control was applied to each tested contrast individually, i.e., it accounts for multiple species being tested but does not account for multiple contrasts and across multiple analysed

visits. When we refer to a “nominal” P value, this indicates that the P value is not subjected to FDR control nor otherwise adjusted for multiple hypotheses.

Broad-sense heritability was determined with ACE model (from R package mets). The model estimates how much the phenotype variation stems from additive genetic effects (A), common environment (C) and unique environment for each twin (E). The model was fitted separately to the abundances of taxa found in more than 2 samples in each arm (*abundance* ~ 1) and used to extract broad-sense heritability.

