### **3. Study Methods**

#### ***Trial Design***

The trial design is described in detail in previously published study protocol ([name] et al., 2021) and briefly described here.

The study is a randomised, placebo controlled, double blinded, intervention study in which participants were grouped into two different arms. One arm received protein food supplement plus prebiotic food supplement and the other arm received protein food supplement plus placebo (maltodextrin). Supplements were posted to participants in pre-mixed identical sachets, which they were advised to take daily for 12 weeks, in a glass of water or other drink. Participants in both groups were also advised to undertake resistance exercises. All participants had a study visit carried out via video teleconferencing software at the beginning and end of the study. They also completed questionnaires, food diaries and cognitive testing remotely at the beginning and end of the study. Lastly the participants also collected biological samples (urine, stool, saliva, and capillary blood) and posted these to the department at the beginning and end of the study. A subset of participants also completed an additional study visit in-person at the department for validation measures.

Randomisation was used to control for equal distribution of key characteristics that may confound between group comparisons. Participants were randomised as twin pairs, with one twin from the pair in the prebiotic food supplement arm and one twin from the pair in the placebo arm. Twin pairs are matched for age and often for sex, early environment, baseline genetic sequence, socioeconomic status etc., proving a strong model for detecting changes while adjusting for both observed and unobserved confounding.

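### Supplementary Figure S2 selects and highlights taxa by the size of an ACE point estimate alone; with 22 MZ and 14 DZ pairs the 0.2 cut is not calibrated against zero heritability, and the displayed mean is biased upward

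*Combined protocol and SAP*

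**What the plan says.** Supplementary Note 1, section 1.1.1.8, describes an intercept-only ACE model (additive genetic, common environment, unique environment) fitted taxon by taxon: "The model was fitted separately to the abundances of taxa found in more than 2 samples in each arm". The caption of Supplementary Figure S2 names the scale: "The model was fitted to the relative abundance of different taxa".

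The caption then sets three rules. The first is the display filter: "Only taxa with broad-sense heritability larger than 0.01 and with prevalence of 2 in twin-pairs were chosen to be included in the figure". The second is the highlight, which goes with a solid line at 0.2: "Taxa with heritability value > 0.2 are shown in brown". The third is the average: "the dashed line marks the mean heritability of the taxa shown in the figure".

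The heritability text in section 1.1.1.8 and the caption contain no test of A = 0, no interval, no multiplicity rule tied to this figure and no reason for choosing 0.2.

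**The concern.** An ACE model separates genetic from shared-environment similarity by comparing MZ with DZ resemblance. With few pairs that comparison is very noisy. The estimate is also bounded below at zero, so noise appears as a pile of zeros plus a tail of positive values. Removing estimates at or below 0.01 discards the pile and keeps the tail.

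Two consequences follow. A point estimate above 0.2 may carry little information about whether a taxon is heritable. And the mean of the remaining taxa is too high by construction, whatever the true values are. At stake is how far the figure can support a statement about which taxa are heritable, or how heritable they are on average.

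**Working it through.** **Inputs from the documents.** Supplementary Table S1 lists 44 MZ and 28 DZ participants. The SAP (section 3, Trial Design) says "Participants were randomised as twin pairs, with one twin from the pair in the prebiotic food supplement arm and one twin from the pair", the second twin going to placebo, so 44/2 = 22 MZ pairs and 28/2 = 14 DZ pairs. The display cut is 0.01 and the highlight cut 0.2. The documents give no null calibration of their own to reproduce.

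**Orientation.** The moment estimate of heritability is 2(r_MZ − r_DZ). For normal data with common correlation ρ (that is, A = 0 and C = ρ), its approximate standard error is 2(1 − ρ²)√(1/22 + 1/14).
- ρ = 0: 2 × √(0.0455 + 0.0714) = 0.68.
- ρ = 0.4: 0.84 × 0.68 = 0.57.

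A cut of 0.2 is about 0.3 standard errors from zero (0.2/0.68 = 0.29; 0.2/0.57 = 0.35). Constrained maximum likelihood behaves differently from the moment estimate, so the rule itself was simulated.

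**Simulation.** The model has MZ covariance A + C, DZ covariance A/2 + C, total variance A + C + E, and all components at least zero. It was fitted by maximum likelihood on a 0.01 grid; against direct optimisation in 60 datasets the median difference was 0.0001 and the maximum 0.008. True A = 0, with 22 MZ and 14 DZ pairs and 3,000 datasets per setting.

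Assumptions, because the documents do not supply them: C from 0 to 0.5; abundance normal, lognormal or lognormal with zeros; with or without the cap at the 97th percentile. Section 1.1.1.8 states that cap for abundance data but does not say whether it reached this fit.

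Share of displayed taxa (> 0.01) that exceed 0.2 when A = 0:

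| Abundance | C = 0 | 0.1 | 0.2 | 0.3 | 0.5 |
|---|---|---|---|---|---|
| Normal | 33% | 43% | 53% | 64% | 67% |
| Lognormal, log-SD 1, uncapped | 47% | 51% | 57% | 67% | 79% |
| Lognormal, log-SD 1, capped | 38% | 44% | 55% | 64% | 78% |
| Lognormal, log-SD 1.5, uncapped | 62% | 63% | 65% | 71% | 80% |
| Lognormal, log-SD 1.5, capped | 42% | 49% | 53% | 61% | 75% |
| 70% zeros, uncapped | 59% | 63% | 66% | 68% | 77% |
| 70% zeros, capped | 39% | 45% | 53% | 62% | 75% |
| 90% zeros, uncapped | 77% | 79% | 77% | 79% | 84% |

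Each entry is P(> 0.2)/P(> 0.01). For normal data with C = 0 it is 8.5%/26.1% = 33%; for 90% zeros with C = 0.5 it is 27.8%/33.1% = 84%. Repeat simulations gave shares as low as 26% for normal data with C = 0.

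**All fitted taxa.** Here 18% to 48% exceed 0.01 and 8% to 37% exceed 0.2; repeat runs reached down to 7%.

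**Null 95th percentile of the estimate.** It is 0.27 to 0.59 for normal data, 0.40 to 0.81 for uncapped lognormal data (log-SD 1) and 0.92 to 0.95 with 90% zeros. It lay above 0.2 in every setting tried.

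**The mean.** Dropped taxa contribute at most 0.01 each, so the mean over all taxa is roughly P(> 0.01) times the displayed mean. For normal data with C = 0, 0.261 × 0.16 = 0.04. The inflation factor is therefore about 1/P(> 0.01), which runs from 1/0.48 = 2.1 to about 5 (1/0.18 = 5.6 is the ceiling). Across all runs the displayed mean under zero heritability was about 0.15 to 0.65, against 0.04 to 0.21 over all fitted taxa.

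**Sample size.** With 220/140 pairs and normal data the displayed share falls to 0% to 31%, and with 2,200/1,400 pairs to 0%. With 18/11 pairs, in case stool samples are missing, it is 36% to 82%.

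**The case against.** The caption only says that taxa are coloured. It declares none of them heritable, and no hypothesis is tested, so the note's false-discovery rule is not breached. Heritability is not among the objectives or outcomes of the protocol or SAP. All of this stands, and it keeps the point minor.

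A reader might infer that most displayed taxa would pass 0.2 even if nothing were heritable. The documents do not support that without conditions. In the table the share is above one half once C is 0.2 or more, or when uncapped data are strongly skewed or sparse. It is below one half for normal or capped data with C of 0 to 0.1. Among all fitted taxa it is always a minority.

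A reader might also infer that the published figure cannot be told apart from noise. That would need the number of taxa fitted, displayed and coloured, and the plotted mean. The figure itself was not available for this check, so those values are unknown, as is whether it carries error bars.

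The runs in the table also leave out the filter on presence in twin pairs. A check that applied the entry filter and required at least two concordant pairs for sparse taxa gave 41% (lognormal, log-SD 1.5) and 45% (70% zeros), both capped with C = 0. The table has 42% and 39%, so the filter does not change the picture.

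**Conclusion.** The point holds as a minor one about an exploratory figure. With 22 MZ and 14 DZ pairs, an estimate above 0.2 does not by itself separate a heritable taxon from a non-heritable one. Under zero heritability, roughly a quarter to four fifths of displayed taxa, or about 7% to 37% of all fitted taxa, would still be brown. Where in that range the trial falls depends on shared environment, skew, sparsity and the cap, none of which the documents state for this fit.

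The upward bias of the mean line is firmer, because it follows from the selection itself. Under zero heritability it amounts to about a two- to five-fold inflation.

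The broad-sense label is a secondary matter. An ACE model has no dominance term, so its A share is additive, that is, narrow-sense heritability. No randomised comparison is affected.

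**What to change.** 1. Compute the mean over all fitted taxa, including those estimated at zero, and report how many were fitted, displayed and highlighted.
2. Show 95% intervals for the displayed estimates, and state so in the caption.
3. Replace the 0.2 cut by a test of A = 0: the likelihood ratio of ACE against CE, with its reference distribution obtained by permuting MZ/DZ labels across pairs, followed by the note's 10% Benjamini–Hochberg rule. With B permutations the smallest P value is 1/(B + 1), so for m taxa B should be at least 10m − 1. At the note's usual 1,000, a single taxon could not pass when more than 100 are tested (0.10 × 1,001 = 100.1).
4. Fit on the centred log-ratio scale that the note already uses for differential abundance, and say whether the cap was applied.
5. Call the quantity narrow-sense heritability.

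The entry filter can stay. "taxa found in more than 2 samples in each arm" means at least 3 + 3 = 6 of 72 samples at one visit (8%), so moving to the note's 10% rule would change little.

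The cost is a re-analysis of existing data and a redrawn figure. The downside is that few or no taxa may remain highlighted.

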## 2.3 Supplementary Figure S3: Taxonomic overview at genus level per sample faceted by twin pair, and by study arm.

[figure not shown]

Bar plots display the relative abundance of the top 10 taxa with highest average abundance across all samples. Light grey (Other) indicates the total relative abundance of metagenomic species that are not in the top 10 most abundant taxa.

**2.4 Supplementary Figure S4: Bray–Curtis dissimilarities among samples stratified based upon whether they are from the same twin pair and from disparate twins pairs**

[figure not shown]

Bray-Curtis dissimilarity is a metric of beta diversity.

**2.5 Supplementary Figure S5: Mann-Whitney U test statistic distributions from comparing Bray–Curtis dissimilarities within and between twin pairs**

[figure not shown]

Original group labels (black line) and from 1,000 group label permutations (green). Left: Baseline, Right: End of study.

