### ***Randomisation/Allocation Concealment/Blinding Procedures***

Participants will undergo computer generated block randomisation in twin pairs by the King's College London Clinical Trials Unit (KCTU). They will be randomised as twin pairs, with one twin in each arm. Researchers and participants will be blinded as to which arm each participant is in.

On completion of the data collection, the KCTU will issue a blinded list denoting what arm each participant is in (Arm 1; Arm 2), but without revealing which arm is the intervention and which the placebo, in order to facilitate blinded analysis to be carried out. Full unblinding will not take place until data analysis is complete. Until that point, only the KCTU will have access to the unblinded information.

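### As described, the study-end twin-similarity comparison does not match its reference on arm: co-twins are always in opposite arms while about half of unrelated pairs share one, so any prebiotic effect on composition would bias it against showing twin similarity

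*Combined protocol and SAP*

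**What the plan says.** The SAP's randomisation section says of participants: "They will be randomised as twin pairs, with one twin in each arm". Its Trial Design section repeats this: "with one twin from the pair in the prebiotic food supplement arm and one twin from the pair in the placebo arm". Every complete co-twin pair is therefore split between prebiotic and placebo.

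Supplementary Figure S4 is titled as showing "Bray–Curtis dissimilarities among samples stratified based upon whether they are from the same twin pair and from disparate twins pairs". Figure S5 shows "Mann-Whitney U test statistic distributions from comparing Bray–Curtis dissimilarities within and between twin pairs", with the panels labelled "Left: Baseline, Right: End of study". S4's caption names no time point; the statement that both visits were analysed rests on S5.

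The method is in Supplementary Note 1, section 1.1.1.8: "Pairwise comparisons of microbiota (dis)similarity were compared using the Mann-Whitney U test and verified by comparing the Mann-Whitney U test statistic obtained" with the original labels against the "test statistic distribution obtained by 1,000 group label permutations". Neither the methods text nor the two captions mentions restricting the reference pairs by arm, stratifying by arm or adjusting for it. The captions of Figures S8 to S10, by contrast, state adjustment for study arm.

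**The concern.** The comparison is meant to show whether co-twins are more alike than unrelated participants. For that, the two sets of distances should differ only in twinship. At baseline they do, because nobody has been treated. At study end they also differ in arm composition: all co-twin distances cross the arms, but only about half of the unrelated distances do. Changing gut composition is the purpose of the intervention, so an arm effect cannot be assumed away.

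If there is one, it enters every within-pair distance and only part of the reference, which pulls the study-end contrast away from twin similarity. At stake is how a weak or null study-end panel, or a drop from the baseline panel to the study-end panel, is interpreted.

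**Working it through.** **Inputs.** 72 participants in 36 twin pairs (Supplementary Table S1), 36 per arm (Table S6), one twin of each pair per arm (SAP). The text gives no U value, no count of distances, no number of study-end stool samples and no arm effect on Bray–Curtis, so there is no figure of the plan's own to reproduce. The images of S4 and S5 were not available; the reading rests on captions and methods text.

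**Counting the pairs (complete data).**
- All pairs: 72 × 71 / 2 = 2,556.
- Co-twin pairs: 36, none same-arm.
- Unrelated pairs: 2,556 − 36 = 2,520.
- Same-arm unrelated: 2 × (36 × 35 / 2) = 1,260.
- Opposite-arm unrelated: 36 × 36 − 36 = 1,260.

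So 0% of co-twin pairs and 50.0% of unrelated pairs share an arm. With incomplete data (assumed 28 to 36 samples per arm) the same-arm share stays between 49.9% and 50.7%.

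**Do the permutations repair this?** Not if they are unrestricted. A shuffled label falls on a same-arm pair with probability 1,260 / 2,556 = 49.3%. The observed co-twin set has none, so the null distribution carries the same mismatch.

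**Size, by simulation.** Assumptions: 36 split pairs, 150 log-normal taxa, the five most abundant shifted in one arm, twin correlation 0 to 0.2, 300 runs per setting, two-sided Mann-Whitney test at 0.05. Arm R² is the raw PERMANOVA value; with no arm effect it is about 1/71 = 1.4%. P is the probability that a co-twin pair is more similar than a reference pair. Detection is the share of runs finding co-twins more similar.

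| Twin correlation | Arm R² | P, all unrelated | P, opposite-arm | Detection, all unrelated | Detection, opposite-arm |
|---|---|---|---|---|---|
| 0.2 | 1.2% (no effect) | 0.642 | 0.642 | 89% | 89% |
| 0.2 | 1.8% | 0.621 | 0.625 | 74% | 77% |
| 0.2 | 3.3% | 0.596 | 0.611 | 51% | 67% |
| 0.2 | 5.4% | 0.569 | 0.599 | 24% | 55% |
| 0.2 | 8.1% | 0.544 | 0.590 | 8% | 42% |
| 0.1 | 1.3% (no effect) | 0.567 | 0.567 | 21% | 21% |
| 0.1 | 3.4% | 0.539 | 0.555 | 8% | 14% |
| 0.1 | 5.7% | 0.516 | 0.547 | 2% | 9% |

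With no twin similarity and R² of 8.4%, P is 0.452 against all unrelated pairs and 0.499 against opposite-arm pairs. Co-twins are then wrongly called less similar in 11% and 0.3% of runs respectively.

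The absolute rates depend on the settings. With four species raised and 200 runs, the mean gap at R² of about 3.5% was understated by about a third with weak twin similarity (0.025 shown as 0.017), 16% with moderate and 11% with strong similarity. At R² of about 1.8% the understatement was 2–7%.

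**What the restriction leaves.** At twin correlation 0.2, take the fall in P from the no-effect value of 0.642:
- R² 3.3%: 0.642 − 0.596 = 0.046 with all pairs; 0.642 − 0.611 = 0.031 with opposite-arm pairs, so 67% of the fall remains.
- R² 5.4%: 0.073 and 0.043; 59% remains.
- R² 8.1%: 0.098 and 0.052; 53% remains.

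The restriction removes the mismatch. It does not remove the arm-related variance added to both sets of distances.

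**The case against.** The strongest reply is that no harm is documented. The reference set is inferred from captions and the absence of a stated restriction; opposite-arm pairs may in fact have been used. The text reports no arm effect on Bray–Curtis and no loss of twin similarity, and the largest biases need an assumed arm effect together with weak twin similarity. The bias also works against the claim of twin similarity, so a positive study-end result would stand all the more firmly. These points stand, and they limit the finding to a conditional one.

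Two further replies stand in part. Change over time has its own display in Figure S7, which follows intra-pair dissimilarity between visits without an unrelated reference, and arm differences in composition are tested separately by PERMANOVA. S4 and S5 are also absent from the SAP's planned tables and figures, and no treatment inference is shown to rest on them. That lowers the weight of the point but leaves the S5 contrast as it is.

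It can also be said that co-twins who diverge under different treatments really are less alike. That is true of the distances themselves. But S5 is labelled as a contrast of within-pair and between-pair distances, and at study end that contrast mixes twinship with arm.

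A reader might infer that the prebiotic effect has in fact been counted as twin dissimilarity, or that co-twins became no more alike than strangers. The documents support neither. Nor does an opposite-arm reference make the two panels fully comparable, as the residual falls above show.

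**Conclusion.** The structural point holds, provided the reference set is what the captions and methods imply. At study end, co-twin distances are all cross-arm, about half of the reference distances are not, and unrestricted label permutations do not correct for this.

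The consequence is conditional on an arm effect that the text does not report. The bias is zero without one, small at R² near 2%, and material when twin similarity is weak and R² is about 3–5% or more. These sizes rest on simulated log-normal compositions and show a range, not an estimate for this trial. The direction is against twin similarity: a positive study-end finding is conservative, while a null finding or a drop from baseline could be misread. The baseline panel is unaffected by treatment, and the primary outcome, chair rise time, is not touched.

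**What to change.** 1. At study end, compare the 36 co-twin distances only with the opposite-arm unrelated distances (1,260 with complete data). Do this in S5, and in S4 if it shows study end.
2. Build the permutation null by randomly re-pairing prebiotic twins with placebo twins and recomputing U each time. Every permuted set is then cross-arm, like the observed one, and the shuffling respects that distances share participants.
3. Apply the same rule to the baseline panel, so that both panels use the same definition.
4. State the reference set and the number of distances in the captions. If opposite-arm pairs were already used, this is the only reference-set change needed.
5. Do not read a remaining baseline-to-end decline as lost twin resemblance on this figure alone; arm-related variance can still lower the contrast. Read it with the intra-pair comparison in S7.

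The cost is a filter on an existing distance matrix, a rerun of the permutations and a caption line. Halving the reference costs almost no precision, because the 36 co-twin distances are the limit. With no arm effect, simulated detection was the same under both references (89% and 89% at twin correlation 0.2).
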